### Inclusion and exclusion criteria

#### Inclusion criteria

(a) Both current PTSD and AUD according to the DSM-5 criteria, for 6 months or longer as assessed via Clinician-Administered PTSD Scale for DSM-5 (CAPS-5) and the Structured Clinical Interview for DSM-5 – Research Version (SCID-5-RV); (b) age >18 years; (c) adequate cognition and English language skills to give valid consent and complete research interviews and assessments; (d) willing to give written informed consent; (e) received prior treatment for PTSD or AUD such as approved psychosocial or pharmacological interventions (given MDMA-assisted therapies are designed to target those that do not respond to traditional therapies); (f) stable housing and (g) able to identify a significant other (such as a family/friend/partner) who could accompany them from the clinic, provide transport and/or be contacted by the study team if required.

#### Exclusion criteria

(a) History of, or currently meeting DSM-5 criteria for a current or lifetime psychotic or bipolar disorders, or major depression with psychotic features, as assessed via the SCID-5; (b) pregnant or lactating (contraception must be used and a sensitive pregnancy test will be performed at baseline and prior to dosing); (c) significant alcohol withdrawal (Clinical Institute Withdrawal Assessment for Alcohol (CIWA-Ar) score ≥10, including history of delirium tremens or alcohol withdrawal seizures); (d) concurrent use of psychotropic medication (antidepressants and alcohol pharmacotherapy use considered for inclusion if assessed by physician and titrated down with 5 half-lives+1 week washout); (e) use of, and unable or unwilling to cease, any medications likely to interact with MDMA in the opinion of the physicians and investigators during the trial (low dose opiates are permitted for pain management but not the night before or after MDMA sessions); (f) current substance use disorder (DSM-5) other than tobacco; (g) abnormal clinical findings including a history of, or current: cardiac disease and/or dysrhythmia, uncontrolled hypertension or severe hypotension, abnormal ECG findings, stroke, liver disease, a history of epilepsy, hyponatraemia or malignant hyperthermia (controlled hypertension and diabetes type II may be permitted) and (h) suicide risk according to clinician judgement and responses to Columbia Suicide Severity Rating Scale-Lifetime (C-SSRS-L) and SCID-5-RV. Details surrounding any previous suicide attempts will be gathered whereby attempts related to their trauma/PTSD and/or associated with the use of psychostimulants will contribute to risk assessment and guide trial safety measures if enrolled; (i) clinically unstable systemic medical (eg, cancer) or psychiatric disorder or condition that might require hospitalisation that precludes trial participation; (j) regular use of ecstasy (at least twice in last 6 months or >10 times within the last 5 years) and (k) enrolled in any other interventional clinical trials in the previous 2 months or over the duration of the study.

### Procedures and schedule of visits

Participants are initially pre-screened either face-to-face by their treating clinician or over the phone by a psychologist or nurse following either self-referral or referral by a medical officer or psychologist. If clinically indicated, participants are offered alcohol withdrawal management services. Eligible participants are then offered further onsite screening for a full eligibility assessment composed of comprehensive medical and psychiatric assessment. The schedule of enrolment, interventions and assessments are depicted in online supplemental table 1.

*Screening visits a and b:* At the onsite screening visits (a and b), participants are asked to provide informed consent by the research nurse. The Participant Information Sheet and Consent Form (PISCF) given to participants clearly outlines the study aims, what is required of the participant and any benefits or risks to participation. Potential participants will be given ample time to review the PISCF and ask questions of their family, friends and/or doctors, prior to providing informed consent. The medical officer performs a physical examination and obtains a structured medical and psychiatric history including management plan for tapering of contraindicated concomitant medications where necessary. Blood and urine samples are taken for clinical laboratory evaluations (see below). The psychologist obtains a structured psychological assessment (see below).

*Baseline visit:* after screening and, if necessary, concomitant medication management is completed, eligible participants undergo a baseline research evaluation.

*Visits 1–3, 6–10, 13–16 (including COPE treatment sessions):* participants receive COPE therapy (see below) delivered by the psychologist the week following their baseline visit and return weekly for sessions. Concomitant medications and AEts (see below) are documented at these visits.

*Visits 8, 16 (medical & research visit):* blood samples are taken for clinical evaluation (liver function tests (LFTs)) and research (phosphatidylethanol (PEth)).

*Visits 4 and 11 (preparation visit):* participant attends a session with the psychologist and co-therapist to prepare for dosing session (see below). Medical review is conducted in view of dosing sessions including examining recent LFTs, concomitant medication and AEs.

*Visits 5a and 12a (dosing visits):* participant attends the dosing session with the psychologist and co-therapist which includes monitoring by the physician and nurse (see below).

*Visits 5b and 12b (integration visits):* participant attends the integration session with the psychologist and co-therapist which includes monitoring and assessment by the nurse (see below).

*Visits 16–18 (follow-up visits):* participants return for the end of treatment review and research follow-up immediately after the final COPE session (visit 16) and then for 6 and 12 follow-up research appointments (visits 17 and 18).

### Medications

Participants will be randomly assigned before dosing to the MDMA or control arm. During dosing sessions, participants randomised to: (1) the MDMA arm will receive MDMA plus placebo (matched to niacin) or (2) the control arm will receive placebo (matched to MDMA) plus niacin. The dosage of MDMA is 80–120 mg MDMA HCl (Dose 1) and 80–160 mg MDMA HCl (Dose 2). PharmAla Biotech, in Canada, will source MDMA (40 mg capsules of MDMA HCl) from Dalton Pharma Services, a good manufacturing practice (GMP)-licenced facility. Placebo contains mannitol (98% w/w), magnesium stearate (2% w/w) and will be sourced by PharmAla Biotech from Psilo Scientific (GMP-licenced). MDMA will be over-encapsulated in gelatine capsules containing mannitol and magnesium stearate. The dosage of active control, niacin (nicotinamide), is 250 mg and will be sourced from Syntro and over-encapsulated with microcrystalline cellulose to look identical to a niacin placebo. Medications are over-encapsulated to maintain the double-blind. A check on the blind is obtained throughout (mid-point and end of treatment) by asking the participant, clinician and the researcher to record the study drug the participant is thought to have received (active drug or active control). The proportion that guessed allocation correctly will be reported in the final results and a sensitivity analysis conducted to determine whether outcomes differ by guessed allocation.

Prior to the dosing sessions, participants will discuss an optional supplemental dose of the study drug with their clinicians. This additional dose will be administered approximately 60–90 min after the initial dose on each dosing day. A singular supplemental dose per dosing session will only be available if: (1) both participant and clinician agree prior to the dosing day, day of dosing and post-initial dose; (2) prior dose was well-tolerated and/or if there are no AEs of concern in the first hour post-dosing, with the AEs of concern being determined by clinician judgement and (3) participant’s vital signs (blood pressure (BP) and heart rate (HR)) remain within standard observational requirements (eg, BP <180/110) or as per clinician judgement (eg, when between BP 160–180/110). Supplemental doses are optional and can be declined by participants or investigators and clinicians at any time. This supplemental dosing schedule is aligned with potential variations in tolerability due to pharmacokinetics and pharmacodynamics and is consistent with the majority of published trials globally.^37^

### Integrated prolonged exposure therapy

COPE represents an integration of existing evidence-based manualised CBT interventions for PTSD and substance use disorders, including imaginal and in vivo exposure, delivered over 12 individual 90 min sessions (total of 19.5 hours).^38^ Although designed to be delivered weekly, flexibility is permitted. More details on COPE session procedures are available in the published *COPE Manual*.^38^ COPE therapists will be Masters-level (or higher) clinical psychologists with extensive training and experience. All study therapists will be involved in regular meetings and receive clinical supervision to discuss participant adherence to treatment and clinical concerns about participants, provide feedback to reduce departure from protocol and assist therapists in identifying issues for subsequent sessions. Therapy sessions will be audio recorded for research and training purposes and randomly selected sessions (25%) will be evaluated with the Yale Adherence and Competence Scale II^39^ to ensure consistency with manual guidelines. Interrater reliability on adherence and competence measures and intraclass correlation coefficients will be calculated. Abstinence from alcohol will be encouraged but not required. Following each session, the participant will complete a brief post-session rating with the Session Rating Scale (SRS).^40^ Recordings of the sessions will be evaluated by the therapists using the Motivational Areas Rating Scale.^41^

### Preparation, dosing and integration sessions

Here we briefly outline the MPATHY preparatory, dosing and integration sessions. More detail is provided in the *MPATHY Therapeutic Dosing Manual* (available on request).

In the preparation component, the COPE therapist is joined by a trained co-therapist. This dyad will then: (1) discuss the details for the day procedure such as length, music, dosing administration procedure, medical monitoring, boundaries of interaction and safety measures; (2) provide some psychoeducation regarding the medications (active control and MDMA); (3) describe the therapeutic approach; (4) revisit techniques from the COPE sessions relevant for the dosing session and (5) explore and clarify the participant’s expectations, intent and hopes of the dosing session including managing expectancy issues, anxieties and alcohol consumption.

Dosing sessions will be conducted in a quiet room with soft ambient lighting and comfortable furnishings. The air-conditioning will be set to an ambient temperature of 20–24°C to ensure a comfortable and safe level. A music soundtrack from WavePath (https://wavepaths.com) will be available. These sessions will be approximately 6 hours in duration. It is a requirement that all participants have a 0.00% breath alcohol concentration at the start of the session or the session will be postponed. Dosing sessions will be audio and video recorded for safety, research and training. Training for these sessions will be provided by clinicians/therapists with experience delivering psychedelic-assisted therapy in clinical trials and clinical supervision. Two people will always be present in the room with the participant on dosing sessions including the COPE-trained clinical psychologist and another appropriately trained co-therapist or staff member (eg, physician, psychologist, experienced research nurse or peer worker). These sessions will thus be unstructured with no therapist-led direction regarding trauma; therapists will keep comments to a minimum and not speak much (to avoid interfering) unless invited by the participant (staying within MDMA-assisted therapy and COPE-aligned therapeutic approaches). All sessions will be audio and video recorded for safety, research and training purposes and will be audited for quality control (eg, fidelity with scripts, language bias re expectancy, etc). Light refreshments will be made available according to a standardised menu plan including sandwich, biscuits and mild/decaffeinated tea or coffee and water (fluid intake will remain <3 L and be spread out appropriately during the session).

The day after each dosing session, participants will attend an ‘Integration Session’ in person with the same dyad. The aim of these sessions is to reflect on the session and discuss the content of the dosing session. More specifically, the Integration Session will entail: exploring and processing cognitions, emotions, sensations and memories that arose during the dosing session; reflecting on key themes; and supporting incorporation into the goals and intention of ongoing therapy aligning with the principles of COPE.

### Study assessments

See online supplemental table 1 for a comprehensive list of study assessments. We will attempt to obtain data for all randomised participants regardless of whether they discontinue treatment and study visits as per intention to treat. Follow-up data may be obtained by telephone.

#### Medical/laboratory tests

These tests screen participants for exclusion criteria, assess potential AEs, provide objective measures of alcohol use and assess covariates and secondary outcome measures. The physical examination at screening includes BP, HR, ECG, height, weight, full blood count, LFTs (bilirubin, Gamma-Glutamyl Transferase, Alkaline Phosphatase, Aspartate Aminotransferase, Alanine Aminotransferase, albumin, protein), coagulation (International Normalised Ratio, Activated Partial Thromboplastin Time), urine toxicology, concomitant medications, withdrawal symptoms (CIWA-Ar). All abnormal findings will be reviewed by the physician, and participation is endorsed or further evaluation performed as clinically indicated. Tests will be repeated if clinically indicated and for baseline measurement if required. PEth is collected at screening/baseline, mid-point (visit 8) and end of treatment (visit 18). Blood samples will also be collected and stored for biochemical and genetic exploratory analyses relating to the current trial and for future use in ancillary studies.

#### Questionnaires and tasks

Demographics, medical history, personal and family history of PTSD and AUD and relevant treatment history will be obtained during screening as in our previous trials.^42^,^47^ The CAPS-5 will be used to obtain diagnosis of PTSD and symptom severity^48^ and the Life Events Checklist for DSM-5 will be used to measure lifetime exposure to potentially traumatic events.^48^ The SCID-5-RV^49^ will be used to obtain AUD diagnosis and gather psychiatric diagnostic information relevant for screening. The C-SSRS-L will be used to screen for suicidal risk in addition to clinician assessment.^50^ The Montreal Cognitive Assessment will be used to screen for cognitive impairment likely to preclude completion of study procedures and treatment (≤24/30 excluded).^51^

The following measures will be implemented at baseline, mid point (visit 8) and end of treatment follow-up: (1) recent (last 30 days) alcohol consumption (frequency/quantity) assessed by the Timeline Follow-Back method (TLFB)^52^; (2) severity of alcohol dependence assessed by the Alcohol Dependence Scale^53^; (3) symptoms of PTSD will be assessed by the PTSD checklist for DSM-5 (PCL-5^48^); (4) severity of symptoms of depression, anxiety and stress assessed by the Depression, Anxiety and Stress Scale (DASS)^54^; (5) recent use of health services assessed by the Health Service Use Questionnaire; (6) sleep disturbance assessed by the Insomnia Severity Index^55^ (ISI); (7) dysfunctional cognitions that may develop following trauma measured by the Post Traumatic Cognitions Inventory (PTCI^56^) and (8) health-related quality of life measured by the Short Form 36 (SF-36^57^). At baseline, major domains of personality will be measured with the NEO Personality Inventory 3^58^; adverse or traumatic childhood experiences will be measured by the adverse childhood experience scale (ACE^59^) and treatment expectancy will be assessed using the Stanford Expectations of Treatment Scale.^60^ The revised Mystical Experience Questionnaire 30^61^ will be administered after dosing sessions to examine mystical, positive mood, ineffability and the Psychedelic Music Questionnaire Short Form will be administered during integration sessions to assess the participants’ experience of music during dosing sessions. At baseline and end of treatment follow-up we will also administer: (1) The Trail Making Test^62^ to measure the speed of processing and executive functioning; (2) Number-letter task (adapted from Rogers and Monsell^63^) to assess working memory; (3) the Emotional Stroop Test will be used to measure attentional biases toward emotional stimuli^64^ and the (4) California Verbal Learning Task to measure learning and retrieval strategies for verbal material.^65^

The TLFB, PCL-5 and C-SSRS will be repeated at each clinic visit (ie, COPE therapy sessions and preparation and integration sessions) to monitor alcohol consumption, symptom improvement and suicide risk. We will also collect daily drinking and mood using Positive and Negative Affect Schedule (PANAS^66^) via Smartphone Ecological Momentary Assessment (SEMA3) for 7 days following the baseline visit and the two dosing sessions.

The SRS will be used in COPE and dosing sessions to measure the quality of the therapeutic relationship and experience of the session.^67^ Therapeutic alliance will be measured by the Helping Alliance Questionnaire^68^ at several time points (visits 4, 8, 11, 16). At end of treatment follow-up, treatment satisfaction will be measured using the Client Satisfaction Questionnaire (CSQ^69^) and the Your Experience of Service (YES^70^) measure.

#### AEs monitoring and management

All AEs reported between consent and final follow-up will be recorded in the electronic case report form. At each visit, the C-SSRS-R will be administered to monitor suicidality, PCL-5 to monitor PTSD symptoms and mood and TLFB to monitor alcohol use. Participants will also be asked at each visit an open question regarding any new physical or mental health symptoms.

During dosing, a medical practitioner and nurse will be on call and participants will be monitored throughout the session according to following: vital signs (BP, HR and body temperature (BT)) taken regularly throughout the dosing session; regular observations aligning with a standardised list used in previous MDMA studies^71 72^; hourly assessment of mood (visual Likert scale 0–10).

During dosing sessions, the following AEs will be addressed accordingly: (1) temperature of >38.5°C: active cooling will commence. This may include fan and/or with ice/cool packs to the groin and axilla. Additional vital sign measurements where appropriate in consultation with the site physician; (2) chest pain, shortness of breath, neurological deficit or confusion: Additional vital sign measurements and intervention where appropriate in consultation with the site physician. Participants would be referred to the hospital emergency department if cardiac or cerebral ischaemia is suspected. Participants experiencing such symptoms would be excluded from subsequent dosing sessions; (3) development tremor or abnormal movements: physician assessment. Medical management of any other AEs will be addressed as per standard procedures of the requisite health setting with additional monitoring and intervention from site physician. Non-medication methods for managing any anxiety will be emphasised. Prior to discharging the participant, BP, HR and BT will be measured. Participants will be discharged when safe and will be escorted home by a nominated significant other (eg, partner/friend/family member). If the participant expresses the desire to leave and cannot gently be encouraged to stay within the designated therapy timeframe they will be medically assessed for safety. If deemed unsafe to leave, they will be requested to stay on routine clinical grounds until they are safe to leave. Overnight hospital stay will be available if clinically indicated. Participants will be advised not to drive or operate machinery for 48 hours after dosing. Participants must refrain from using low dose opiates for pain management for the evening post-dosing. If a participant exhibits any signs of toxicity, they will not receive another dosing session. If the participant reports adverse psychological symptoms, they are not required to receive another dosing session.

In the day following each dosing session (integration) and at the next visit, AEs will also be collected using the Systematic Assessment for Treatment Emergent Effects (SAFTEE) interview,^73^ a widely used measure of AEs and for which a standardised approach exists for trials of medication for AUD. At the integration session symptoms such as mood, alcohol consumption, sleeping and suicidality are monitored. During the week following each dosing session, regular phone calls with participants will discuss any AEs or changes to concurrent medications. Participants will also be asked to complete the PANAS three times a day for the week and record alcohol consumption using the SEMA software. Desire to use illicit ecstasy will be monitored with specific questions pertaining to this issue asked in the following COPE sessions.

#### Data and safety monitoring

AEs are collected at every study visit and the site investigator rates their relationship to medication. Serious AEs are defined as by the Therapeutics Goods Administration.^74^ If serious or unexpected AEs occur during the trial, they are reviewed by the principal investigator and the trial team and reported within the specified time frames to the lead hospital ethics review committee and to the Data and Safety Monitoring Board (DSMB). The DSMB comprises three members independent of the research study and funding body and meets regularly to provide oversight and monitoring to ensure participant safety and trial validity and integrity. The DSMB can request that the trial be terminated by the principal investigator in the event of safety concerns. Participants are assigned a code and their information de-identified in password protected documents.

#### Outcomes

##### Primary

The primary outcome is PTSD symptom severity as assessed by the CAPS-5 from baseline to end of treatment (visit 16). CAPS-5 is a structured diagnostic interview with excellent psychometric properties and diagnostic efficiency and used widely in MDMA-assisted PTSD studies. The CAPS-5 will be administered by independent evaluators blind to treatment condition. We will also examine secondary PTSD outcomes including change in self-reported PTSD symptom severity via the PCL-5 from baseline to visit 16. PCL-5 has excellent psychometric characteristics for a secondary indicator of PTSD symptom severity.

##### Secondary

The secondary outcome will be alcohol consumption expressed as self-reported number of heavy drinking days (HDDs) per week, defined as >4 drinks for women, ≥5 drinks for men (where a single standard drink is defined by 10 g of ethanol). Any conflicting information will be validated by collateral reports (provided by electronic medical records or clinicians) and measurement of biological markers of alcohol consumption (PEth). We will also examine absence of any HDDs per week over treatment period and standard drinks per drinking day (DDD).

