**Methods and analysis:**

This world-first double-blind trial will aim to randomise 100 participants with PTSD+AUD to a regimen of Concurrent Treatment of PTSD and Substance Use Disorders Using Prolonged Exposure (COPE) (12 sessions)+MDMA (80–160 mg: 2 dosing and 2 integration sessions) or COPE (12 sessions)+active control (niacin 250 mg: 2 dosing sessions and 2 integration sessions). All participants will receive medical management. The primary PTSD outcome will be the clinician-administered PTSD Scale for DSM-5. The primary drinking outcome will be the number of heavy drinking days (HDDs) per week, validated by phosphatidylethanol. Secondary PTSD and alcohol-related outcomes will include PTSD checklist for DSM-5 scores, absence of any HDDs and standard drinks per drinking day. We will also examine change in other clinical conditions and symptoms including depression, sleep disturbances and post-traumatic cognitions; treatment satisfaction and engagement; adverse events; and cost-effectiveness.

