### Statistical analysis

All available participant data will be employed to follow intention-to-treat principles. Participants will be followed irrespective of whether they continue to receive treatment. We obtained a retention rate of ~90% for assessments in our most recently completed alcohol pharmacotherapy trial.^47^ Nonetheless, as with all alcohol and/or PTSD treatment studies, we anticipate intermittent missing data which will be handled through use of multiple imputation (if appropriate, following investigation of the mechanism causing data missingness, see Jakobsen *et al*^75^) and assessed via sensitivity analysis. MDMA versus control will first be compared over repeated measures of the primary outcome, CAPS-5 score, followed by the secondary outcome, HDD frequency/week, using mixed effects models for continuous and count responses respectively (models can also be extended to allow for zero inflation where required). Other outcomes will also be examined using mixed models, adjusted for multiple comparisons. Additional covariates and predictors will be included for sensitivity analyses. Similarly, as per our prior work,^43 76^ we will also examine predictors of response (eg, sex, treatment expectancy, severity of AUD and/or PTSD).

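### The sex-specific heavy-drinking-day cut-offs (>4 drinks for women, ≥5 for men) select the same days when drinks are counted whole; the intended rule should be stated before unblinding

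*Protocol article*

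**What the plan says.** The Secondary subsection of Outcomes gives the only definition of a heavy drinking day in the article: "defined as >4 drinks for women, ≥5 drinks for men". The unit follows in the same sentence: "where a single standard drink is defined by 10 g of ethanol". No rounding rule is given, and the text does not say whether counts are whole numbers.

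The cut-off feeds two outcomes:

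- **Heavy drinking days per week.** The Abstract says "The primary drinking outcome will be the number of heavy drinking days (HDDs) per week, validated by phosphatidylethanol". The Outcomes section says "The secondary outcome will be alcohol consumption expressed as self-reported number of heavy drinking days (HDDs) per week". The Statistical analysis section takes it second, after CAPS-5: "followed by the secondary outcome, HDD frequency/week, using mixed effects models for continuous and count responses respectively". Whichever label is used, it is the trial's main alcohol measure.
- **Having no heavy drinking days.** The Abstract lists it: "Secondary PTSD and alcohol-related outcomes will include PTSD checklist for DSM-5 scores, absence of any HDDs and standard drinks per drinking day". The Outcomes section repeats it for the treatment period.

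Drinks per drinking day, the other alcohol outcome, does not use the cut-off.

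**The concern.** A definition with different numbers and different operators for women and men announces a sex difference. Here a strict inequality at 4 is paired with a non-strict inequality at 5. For whole numbers these are two ways of writing the same condition, so the rule does not deliver the difference it sets out.

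What is at stake is which days count as heavy. If one side is misstated, every day exactly at that boundary is scored differently from what was intended, in one sex only. That changes the level of weekly heavy drinking days in that sex, and one such day is enough to change a participant's status on the outcome of having none. Sex at birth is a stratification factor, and sex is named as an example of a predictor of response, so results by sex may well be read. If the wording is noticed only at analysis, the choice of repair would also be made late, on the main drinking outcome.

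**Working it through.** **Inputs, all from the Secondary subsection of Outcomes.** Let x be standard drinks in a day, with 1 drink = 10 g of ethanol.

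- Women: heavy if x > 4, that is, more than 4 × 10 = 40 g.
- Men: heavy if x ≥ 5, that is, 5 × 10 = 50 g or more.

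**Step 1: whole drinks.** For integer x, x > 4 holds exactly when x ≥ 5. Comparing the two rules at every whole count from 0 to 60 gives no count that is classified differently.

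**Step 2: fractional drinks.** The rules disagree only where 4 < x < 5 (more than 40 g and less than 50 g). In steps of 0.5 the one disagreement is 4.5; in steps of 0.25 they are 4.25, 4.5 and 4.75; in steps of 0.1 they run from 4.1 to 4.9.

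| Drinks | Grams | Woman | Man |
|---|---|---|---|
| 4 | 40 | not heavy | not heavy |
| 4.5 | 45 | heavy | not heavy |
| 5 | 50 | heavy | heavy |
| 6 | 60 | heavy | heavy |

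**Step 3: what a repair would move.** These variants are illustrations, not proposals, since the article does not show what was meant.

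- If the women's rule were x ≥ 4, whole-drink scoring would change only for days of exactly 4 drinks (40 g), in women.
- If the men's rule were x > 5, it would change only for days of exactly 5 drinks (50 g), in men.
- Either variant separates the sexes by one whole drink.
- If one common rule of x ≥ 5 were meant, no whole-drink day changes in either sex. The only change is in women, for totals strictly between 4 and 5.

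**Step 4: size.** For one participant, the change in heavy drinking days per week equals the number of days that week exactly at the moved boundary, so it lies between 0 and 7. As an extreme example, a woman who drinks exactly 4 drinks every day has 0 heavy drinking days per week as written and 7 under x ≥ 4. The average change in a sex is the share of drinking days at the boundary multiplied by drinking days per week. The article gives neither quantity, so no average can be calculated.

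**Step 5: what does not depend on the cut-off.** The Sample size calculations section rests on CAPS-5 alone, so the 50 per arm and the power statement are unaffected.

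**The case against.** The strongest reply is that the rule can be executed as written: it classifies every quantity in each sex without ambiguity, and because drinks are defined in grams, fractional totals are possible and the two rules then differ. This stands as far as it goes. It does not explain why a deliberate sex difference would be confined to part of one drink, and the article gives no rationale or rounding rule that would make sense of it.

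A reader might infer more than the text supports, in three ways.

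- **That one threshold is certainly wrong.** This is a strong inference, not a proof. A common five-drink cut-off may have been intended; then neither side is wrong for whole drinks and only the notation is clumsy.
- **That the treatment comparison is biased.** Nothing shows this. The same rule applies in both arms, the trial is planned as double-blind, and randomisation is stratified by sex at birth. Moving the cut-off changes what is counted, and so what the outcome measures, but by the same rule for MDMA and control.
- **That the analysis of sex as a predictor is biased.** A different cut-off would change the level of the drinking outcomes in one sex. That does not by itself distort a sex-by-treatment comparison. The Statistical analysis section lists sex only as an example, and does not say that response there means heavy drinking days.

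It is also true that an article condenses a fuller protocol. But the objection here is to a complete sentence, with its operators, numbers and unit all present, and not to detail left out.

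**Conclusion.** The point holds in a limited form. The article's only definition of a heavy drinking day sets out two sex-specific thresholds that coincide for every whole number of drinks and differ only strictly between 4 and 5. That much is arithmetic and needs no assumption. Either an operator or a number is misstated, or the sex split is redundant, and the document does not allow a choice between these.

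The consequence is confined to the scoring of boundary days in heavy drinking days per week and in the outcome of having none, including their level by sex. How many days are involved is unknown. The point does not threaten the trial's primary conclusion on PTSD severity, but it concerns the main drinking outcome and should be settled before anyone can see which repair favours which result.

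**What to change.** Before any unblinded look at the data:

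1. Reconcile the definition. State both thresholds with the same operator and in grams as well as drinks, or state one common threshold and remove the sex split. The sponsor has to say which was intended.
2. State one rule for fractional drinks (for example, whether grams are used unrounded) and apply it identically in women and men.
3. Rescore the days already collected. The Timeline Follow-Back records quantity as well as frequency, so the stored quantities can be reclassified.

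The cost is one sentence in the protocol and one line of derivation code. No new data are needed and the sample size does not change. The Participant recruitment section says that recruitment is under way with completion expected in 2027, which suggests there is time to do this.
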